#### 2.2.2. Effectiveness Measures

The effectiveness measures will be collected at pre-test, post-test, and follow-up. These measures are described as follows:

Stress. The first measure is related to the levels of perceived stress during the past month, which will be evaluated through the Perceived Stress Scale (PSS) [49,50]. This questionnaire contains 14 items (e.g., “In the last month, how often have you felt nervous or stressed?”). The scale of Likert responses ranges from 0 = *never* to 4 = *very often*, where 4 means the highest level of perceived stress. The instrument score is obtained from the mean of the scores, whose values range between 0 and 4. Research on the reliability and validity of this instrument shows internal consistency and validity, with a reliability value of α = 0.81.

Mindfulness. The second measure will be the evaluation of the levels of mindfulness and awareness in the present moment over a short period of time through the Mindfulness Attention Awareness Scale (MAAS) [51,52]. This instrument is composed of 15 items (e.g., “I do things quickly and hastily without paying much attention to what I am doing”), and uses a 6-point Likert scale, between 1 = *almost always* and 6 = *almost never*, where higher scores indicate a higher degree of mindfulness. The instrument score is obtained by calculating the mean of the scores, whose values range between 1 and 6. Research on the reliability and validity of this instrument has shown high internal consistency, with a Cronbach’s alpha of α = 0.88, and with significant values of criterion and discriminant validity.

Emotional Intelligence. The third measure is related to emotional intelligence, which will be assessed using the Emotional Quotient Inventory Short Form (EQi) [53,54,55]. This scale has 35 items (e.g., “When facing a problem, the first thing I do is stop and think”), which are divided into 4 subscales: intrapersonal intelligence, interpersonal intelligence, adaptability, and stress management. The response to the items is on a Likert-type scale, ranging from 1 = *very rarely true in me* to 5 = *very frequently true in me*. The score of the instrument is obtained from the means of the items belonging to each subscale, whose values range between 1 and 5. The reliability data of the instrument are acceptable in all subscales: 0.73 in the intrapersonal dimension, 0.78 in the interpersonal dimension, and 0.70 and 0.75 for adaptability and stress management, respectively.

General Health. The fourth measure will consider the general aspects of the symptoms regarding general health in recent weeks, which will be measured with the General Health Questionnaire (GHQ) [56,57]. This questionnaire consists of 28 items (e.g., “Have you felt perfectly well and in good shape?”) grouped into 4 subscales of 7 items each: somatic symptoms, anxiety and insomnia, social dysfunction, and severe depression. The responses range from 0 = *not at all* to 3 = *much more than usual*, and the instrument score is obtained via the means of the items belonging to each subscale, whose values range between 0 and 3. This instrument has shown high test–retest reliability (*r* = 0.90) and satisfactory data regarding predictive validity.

Parental Role. The fifth measure refers to the perception of efficacy of the parental role, which will be evaluated with the “Me as a Parent” (MaaP) scale [58]. This instrument has 16 items (e.g., “I trust myself as a parent”), which measure 4 factors of 4 items each: self-efficacy, personal agency, self-reliance, and self-management. The items have Likert-type responses that range from 1 = *strongly disagree* to 5 = *strongly agree*, where the highest scores reflect higher levels in each construct; thus, in order for the personal agency factor to have the same measure, the responses to the items must be reversed. Mean scores can range from 1 to 5 on the general scale and on each of the subscales. The data on the reliability of the global scale show good internal consistency (α = 0.85), and the data referring to facial, factorial, and convergent validity are also satisfactory. Regarding the reliability of the subscales, they all have α values above 0.60.

#### 2.2.3. Perceived Impact by the Participants and Implementation Analysis of the Program

In order to evaluate the perceived impact by the participants and the implementation of the program, halfway through the intervention, in the sixth session, the participants will fill out a questionnaire composed of nine open questions designed ad hoc to obtain feedback from the participants on the intervention process (Table A2). The questions will refer to the expectations met up to that moment, the learning obtained and its integration into daily life, the changes perceived, the implementation of the practices, the difficulties encountered, and the methodology used (e.g., “Do you notice changes in the physical body/mind as a result of these practices?”). These questions were based on the mid-program questions proposed in the original MBSR; the authors then adapted them to the program and intervention context, incorporating questions considered relevant by the authors—who have experience in program evaluation—to adequately fit the characteristics of this intervention. The open questions were developed so that they were relevant, clear, concise, and specific, without overlapping with others. Finally, a practitioner with experience in mindfulness interventions reviewed the questions and adapted their language and formulation [59].

Moreover, the professional who leads the group will fill out a field diary after each intervention session, where information will be collected about the implementation of the program, as well as the group dynamics and the implementation of informal practices at home (Table A3). The questions will have both open and closed answers (e.g., “Any notable issues in the session? Strengths of the program, aspects of the program that have not worked well, or other observations about the course of the session”).

A discussion group will be carried out at post-test (in the last session), in which the following questions will be presented: (a) “Are you satisfied with the program? What has it given you in a personal and professional context?”; (b) “What are the elements or components of the program that have helped you the most? Why?”; (c) “What do you think about the intervention being carried out in a group? Has it helped/contributed or not? In what way?”; (d) “What moments in the intervention would you consider to be the turning point for you?”; and (e) “What do you think could be improved about the program in the future?”.

Finally, with the aim of evaluating the application of the learning to daily life achieved through participation in the intervention, the participants will fill out a questionnaire 6 months after the end of the intervention, in the follow-up phase (Table A4). This questionnaire will be made up of both of open and closed questions (e.g., “In what aspects have you included mindfulness into your daily life? What has helped you to do so?”).

#### 2.2.4. Client Satisfaction

This evaluation will be carried out using the Client Satisfaction Questionnaire (CSQ) [60,61], which is composed of eight items (e.g., “How would you rate the quality of the service you have received?”), each of them with a 4-point Likert-type scale. The weighted score ranges between 1 and 4, with the highest scores indicating the highest satisfaction. Research on the psychometric properties of the instrument indicates good internal consistency (α = 0.93) and concurrent validity [60].

### 2.3. Study Setting

The implementation of the MBSR-P will be carried out in the specialized mental health facilities for children and adolescents of the region where the study will take place. In this region, mental health services offer specialized programs of mental health care for the population that needs it, including children and adolescents. The portfolio of care programs in this resource is made up of outpatient care, day programs, and full hospitalization [62,63].

In these specialized services, the patients regularly visit hospital facilities and dedicate a large amount of time to health care. This immersion sometimes causes personal wear and stress, especially for the patients’ relatives, and specifically for the main caregivers (mostly parents), who must face added and unknown responsibilities. For this reason, it is of great relevance not only to attend to the patients, but also to provide professional attention to the people who accompany them, in order to minimize the negative impact on their lives and allow them to reconcile the latter in a positive way.

### 2.4. Participants

#### 2.4.1. Characteristics

The study sample will be made up of caregivers of children with a mental disorder who receive attention from specialized mental health services.

In this context, the professionals who work in that specific hospital unit have observed the overload of caregivers due to the high responsibility involved in taking care of their children in their particular circumstances, thereby corroborating the need to provide care for caregivers [4].

The care proposal from the mindfulness program emphasizes taking care of oneself in order to be able to take care of others in an effective way, through the use of strategies that help to manage difficult day-to-day situations, which are sometimes a source of stress for parents. Emphasis is placed on the relationship with oneself and on the acceptance of one’s own feelings, so as to then focus on communication and conscious relationships with the person(s) cared for.

In general, this protocol seeks to provide complementary care for informal caregivers who seek to contact other caregivers who live the same experience, with the aim of being able to share it and learning other ways to cope with their circumstances and to activate internal resources as a means to overcome stress, pain, and daily challenges. Likewise, it is intended to give parents the opportunity to optimize their parental performance.

#### 2.4.2. Recruitment, Inclusion, and Exclusion Criteria

For the selection of the sample, a non-probabilistic sampling will be carried out by accessibility to the target population. The participants will be informed of the intervention through posters that will be placed in the waiting room of the specialized mental health services for children and adolescents, and through the health care professionals who work in that service and who care for the families. The professionals will inform the caregivers who, in their opinion, could benefit from participation, referring them to the program, thus promoting the participation of parents with higher support needs, and complementing the previous recruitment method. After being duly informed and knowing the most relevant points of the program, the caregivers who are interested in carrying out the intervention will voluntarily fill out a document with their identification data and deliver it to the hospital administration to record their registration. The professional who will implement the program will contact the interested people in order of request, prioritizing parents who are referred to the program by the mental health professionals, and will invite them to an informative meeting about the program to provide a first contact and explain what the program would consist of and its purpose.

The inclusion criteria for participation are: (1) being a caregiver for a child with a mental health disorder and receiving care from the specialized mental health services for children and adolescents; (2) not having previously participated in the same MBSR group; (3) not experiencing a major life crisis; (4) not having suicidal ideas at the time of intervention; and (5) not showing signs of addiction to toxic substances.

Since randomization of the groups will not be possible, the control group will be made up of subjects comparable to the intervention group in terms of their sociodemographic profiles, via a matching strategy aimed at guaranteeing equivalence between groups [46]. We will consider three different variables to match the control group: (1) age of the child, divided into two categories (children or adolescents); (2) diagnostic category of the child (differentiating between externalizing disorders, internalizing disorders, or others); and (3) sex of the parent. Parents enlisted in the waiting list to participate in the intervention will be used as the control group in order to guarantee recruitment and retention.

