#### 2.5.3. Sample Size

To calculate the sample size necessary to achieve adequate statistical power in the evaluation of the program, the G*Power 3.1 program was used [66]. Two calculations were made for the sample size. The first calculation that was carried out for the pre-test and post-test analyses was made a priori for ANOVA analysis of repeated measures within–between interaction, with a mean Cohen effect size *f* = 0.25 [67] and α = 0.05, two groups with two temporal measures, correlation between the measures of 0.50, and sphericity of 1. With these assumptions, to achieve the acceptable minimum Cohen effect size of 0.80 [68] and obtain a statistical power of 0.80, the sample should consist of at least 34 participants. Although regarding the size of the control group, following a common knowledge rule in program evaluation, the control group should be composed of a minimum of (*n*/2) + 1—where *n* is the sample size of the group of participants—in this study, a minimum of 20 participants is established for the control group, with the objective of reaching the recommended size for the parametric tests [69].

The second sample calculation that was carried out for the follow-up analysis of the intervention group was performed a priori for the ANOVA analysis of repeated measures within factors, with a mean Cohen effect size *f* = 0.25 [67] and α = 0.05, a group with three temporal measures, correlation between the measures of 0.50, and sphericity of 1. With these assumptions, to achieve the acceptable minimum Cohen effect size of 0.80 [68] and obtain a statistical power of 0.80, the sample should be made up of at least 28 participants.

Among the analyses that were conducted, the most restrictive was the first calculation referring to pre-test and post-test measures of the intervention group and the control group; thus, we assume that the study sample must consist of at least 34 participants for the intervention group and 20 participants for the control group.

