### 2.6. Data Analysis

#### 2.6.1. Quantitative Data

The analysis of the quantitative data will be carried out using the statistical program SPSS v-21 (IBM Corp., Armonk, NY, USA) [70]. Firstly, missing data at the level of the Likert scale questionnaires will be studied. Little’s MCAR test will be used to verify whether missing data per questionnaire are below 10%, which will mean that they are randomly distributed. If this assumption is met, it will also be verified whether missing data per item have a percentage below 5% and, if so, the data will be imputed through the SEM procedure using the expectation maximization (EM) algorithm from SPSS. For those cases with missing data at the questionnaire level, the cases will be discarded [71].

The distribution of the values will also be evaluated through asymmetry and kurtosis, and the presence of extreme cases in the variables studied will be examined by analyzing the interquartile ranges through stem and leaf graphs [72].

Moreover, other statistical assumptions for the parametric tests will be checked and reported (i.e., sphericity, normality, linearity, homogeneity, and absence of multicollinearity and singularity) [73]. If the sphericity assumption is not fulfilled, the *F*-test will be adjusted as an alternative for analysis with the Greenhouse–Geisser index, reducing the degrees of freedom associated with the *F* statistic of the ANOVA as a function of the corrective factor ε [74]. If normality violation occurs, parsimony transformations will be applied to correct the non-normal distributions [75]. If multicollinearity applies, composited factors will be computed for those involved variables.

The sociodemographic variables will be used to describe the samples, to control for them in the main analyses, and to achieve equivalence between the characteristics of the control group and those of the intervention group. Both descriptive and correlational analyses will be performed as preliminary analyses.

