The effectiveness of the MBSR-P intervention will be examined by performing two-way repeated measures ANOVA for each effectiveness dimension studied, with the group (0 = *control*, 1 = *intervention*) as the factor. Interaction effects will be examined. *R*^2^ will be computed as the effect size index, and will be evaluated according to the conventional levels of 0.01, 0.06, and 0.14 for the small, medium, and large effect size levels, respectively [67]. The corrected *R*^2^ will be calculated taking into account the within- and between-subjects errors [75]. In the event that the assumptions for these analyses are not fulfilled (e.g., if normality is violated and not able to be fixed by variable transformations), Wilcoxon’s non-parametric tests will be used as an alternative [74]. Mean and standard deviation will be provided for participants’ satisfaction, and for the implementation of information registered in the field diaries.

Figure 2 shows the steps that will be followed for quantitative data analysis.

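### Referred, higher-need parents get places first and the waiting list supplies the controls; neither matching nor adjustment covers referral route or baseline outcome, so differential regression to the mean can be counted as programme effect

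*Protocol article*

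**What the plan says.** All references are to the protocol article.

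- **Access (2.4.2).** Professionals refer caregivers who they think could benefit, "thus promoting the participation of parents with higher support needs". Interested parents are then contacted in order of request, "prioritizing parents who are referred to the program by the mental health professionals".
- **Controls (2.4.2).** "Since randomization of the groups will not be possible, the control group will be made up of subjects comparable to the intervention group" on sociodemographic profile. The source is the queue itself: "Parents enlisted in the waiting list to participate in the intervention will be used as the control group".
- **Matching (2.4.2).** "We will consider three different variables to match the control group": child age band, child diagnostic category and sex of the parent. The stated aim is equivalence between the groups.
- **Adjustment (2.6.1).** "The sociodemographic variables will be used to describe the samples, to control for them in the main analyses". Table A1, which lists those variables, has no item on how the parent came to the programme.
- **Effectiveness analysis (2.6.1).** "two-way repeated measures ANOVA for each effectiveness dimension studied", with group as the factor and the interaction examined.
- **Limitations (3.2).** The lack of randomisation is acknowledged. Need-based priority is not mentioned.

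**The concern.** The access rule can sort the two groups on need. If referred parents take places first, the waiting list may hold relatively more parents who came through the posters and whose need is lower. None of the three matching variables captures this, and neither does any sociodemographic covariate in Table A1.

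With two measurements, the group-by-time interaction is a comparison of change scores. It cancels a stable difference between the groups. It does not cancel a difference that is partly temporary, because a group measured at a high point tends to fall back without any intervention. Perceived stress covers the past month and general health covers recent weeks (2.2.2), so both can move in this way. Where it happens, the bias would normally favour the programme.

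This is the article's only between-group comparison, and it carries the effectiveness objective in 1.5.

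**Working it through.** **Inputs from the article (2.5.3).** Effect size f = 0.25, α = 0.05, power 0.80, two groups, two measurements, pre-post correlation ρ = 0.50, and planned groups of 34 and 20. **Not given:** the baseline gap between the groups. It is assumed here and varied.

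**1. The plan's own figure.** For the within-between interaction, λ = f² × N × m / (1 − ρ). With N = 34 in total and m = 2, λ = 0.0625 × 34 × 2 / 0.5 = 8.5, which gives power 0.807. The stated 34 reproduces. The second calculation (one group, three measurements) also reproduces: 28, power 0.812.

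**2. The design effect as a difference in change.** The SD of change is √(2(1 − ρ)) = √1 = 1.0 baseline SD at ρ = 0.50. With 17 per group, √8.5 = 2.915 = D / √(2/17), so D = 1.0 SD. This is the yardstick for the bias.

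**3. Spurious change under no programme effect.** If selection acts on the observed current score, the expected differential change is (1 − ρ) × gap. At 34 versus 20 the standard error is √(1/34 + 1/20) = 0.282 SD when ρ = 0.50. The two-sided rejection rates come from the noncentral t with 52 degrees of freedom.

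| ρ | Assumed gap (SD) | Spurious change (SD) | False-positive rate |
|---|---|---|---|
| 0.50 | 0 | 0 | 5.0% |
| 0.50 | 0.25 | 0.125 | 7.2% |
| 0.50 | 0.50 | 0.25 | 14.0% |
| 0.50 | 0.75 | 0.375 | 25.7% |
| 0.50 | 1.00 | 0.50 | 41.4% |
| 0.30 | 0.50 | 0.35 | 17.8% |
| 0.70 | 0.50 | 0.15 | 10.4% |

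**4. The two extremes.** If the gap reflects only stable need, nothing regresses and the rate stays at 5%. If the gap is wholly transient, all of it regresses, not half. A 0.25 SD gap then gives 0.25 SD (14.0%) and a 0.50 SD gap gives 0.50 SD (41.4%), with the change SD held at 1.0. So (1 − ρ) × gap is not an upper bound.

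**5. Simulation of the priority rule.** Assumptions: 54 applicants, 34 places given to referred parents first, 30% or 60% referred, no programme effect, ρ = 0.50, and a correlation of 0.3 or 0.5 between the referral judgement and need.

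- *Referral follows the current score.* The gap is 0.24 to 0.75 SD and the spurious change 0.12 to 0.37 SD. The change-score test rejects in 7% to 26% of runs. Baseline adjustment (ANCOVA) has bias of about zero and rejects in about 5%.
- *Referral follows stable need.* The gap is 0.17 to 0.53 SD, the spurious change is about zero and the change-score test rejects in about 5%. ANCOVA is now biased against the programme by 0.08 to 0.28 SD and rejects in 7% to 20%.

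Each analysis is therefore safe in one situation and biased in the other.

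**The case against.** A reader might infer that regression to the mean *will* inflate the result. The article does not support that, for these reasons:

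- Referral rests on professional opinion about who could benefit. No score, cut-off or acute trigger is stated, so selection at a temporary peak is a possibility and not a documented fact. Higher support needs may well be chronic, and the interaction test removes stable differences.
- Parents in a major life crisis or with suicidal ideas are excluded, which trims acute extremes.
- The pre-test is taken at the first session (2.5.2), after registration and invitation, so part of any elevation at referral may already have faded.
- Parents who register from a poster may also do so at a bad moment. Only the differential matters.
- The make-up of the waiting list is unknown. If referrals exceed places, referred parents will be on it too.

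All of this stands against certainty and against any single figure for the bias. It does not remove the mechanism, because nothing in the stated matching or adjustment would detect or correct it.

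Two further points limit the remedy. Matching already has 2 × 3 × 2 = 12 cells for 20 controls, and strict matching on a fourth binary variable makes 24, which may not be feasible. If route nearly coincides with group, adjusting for it costs precision and separates little. Also, requiring the change-score and adjusted results to agree before claiming effectiveness could block a true effect when need is stable. That would be a trade-off, not a necessary condition.

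Referral route must be known to staff for the priority to be applied. Its absence from Table A1, a questionnaire for parents, does not show that it is unavailable, only that the article does not plan to use it.

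**Conclusion.** The point holds as a risk that the plan leaves uncontrolled. Access depends on referral for need, the comparison group comes from those still waiting, and the stated matching and covariates include neither referral route nor baseline outcome. The group-by-time result can therefore contain differential regression to the mean.

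The size is not computable from the article, because it depends on an unstated gap and on how much of that gap is temporary. With selection on the current score, ρ = 0.50, groups of 34 and 20, and an assumed gap of 0.25 to 0.75 SD, the spurious change is 12.5% to 37.5% of the 1.0 SD design effect, and the false-positive rate is 7% to 26% instead of 5%. It is about zero if need is stable and larger than this range if the gap is wholly transient. The sample-size figures are not affected. The limitation on randomisation in 3.2 does not cover this point, since it does not say that access is ordered by need.

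**What to change.** 1. Record referral route (professional or poster) at registration.
2. Where numbers allow, draw controls first from referred parents who are still waiting. The priority rule itself need not change.
3. If the groups overlap on route, balance on it or adjust for it. If they do not, report route by group and do not force a fourth strict matching variable.
4. Report baseline standardised differences on the outcomes and on route, and do not rely on matching to deliver equivalence.
5. Prespecify a baseline-adjusted (ANCOVA) estimate as a sensitivity analysis beside the change-score result, and interpret disagreement between the two as possible selection bias.
6. Add need-based priority to 3.2, next to the lack of randomisation.

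The cost is one extra field, one extra model and fewer close matches per control. Route needs to be recorded from the start, because reconstructing it afterwards may not be reliable.
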